#### PCR genotyping

One milliliter of blood is drawn on day 1 if malaria-positive and at recurrence. PCR genotyping of *msp1*, *msp2*, and *GLURP* genes is performed to identify the unique fingerprint of the infecting parasite and any subsequent development of malaria after therapy in order to determine if it is a recrudescent infection or new infecting genotype [22]. Gametocyte PCR and molecular marker analysis is performed as previously described [23–26].

#### G6PD testing

On enrollment, volunteers are assessed for G6PD deficiency with both fluorescence (qualitative) and quantitative testing, and one or more commercially available point-of-care test kits, and correlated with single nucleotide polymorphism analysis for G6PD gene mutations. Approximately 1.5 mL per blood draw is collected in an EDTA (anticoagulant) tube for this purpose.

Venous blood is tested for qualitative G6PD activity using the fluorescent spot test method, as recommended by the International Committee for Standardization in Hematology using commercially available kits (R&D Diagnostics Ltd., Greece). This method detects fluorescence of the enzyme NADPH under long-wave (365 nm) UV light. Reduction of NADP to NADPH occurs in the presence of G6PD. The rate and extent of NADPH formation is proportional to G6PD activity. Normal samples fluoresce brightly, whereas deficient samples show little or no fluorescence [2].

Quantitative testing will be performed using an FDA-approved test kit (e.g., Trinity Biotech, Ireland) and results will be calculated based on same-day hemoglobin values from the CBC. Severe deficiency (WHO class I or II) will be defined as 10% or less of the lower limit of normal activity (in G6PD activity units per gram of hemoglobin) established for the quantitative assay system. Subjects with severe deficiency will be enrolled in the study as this is not an exclusion criterion; class I–V deficiencies are permissible for enrollment. To evaluate the performance of a commercial G6PD deficiency RDT in malaria patients from Cambodia, the CareStart™ G6PD test is being compared to the “gold standard” G6PD enzyme quantitative test for their potential use as point-of-care diagnostics for G6PD deficiency. However, no clinical decisions will be made based on the results of either point-of-care test in this study.

#### Permethrin clothing treatment

Each uniform is treated by study staff according to the site’s randomization prior to distribution with a single application of the 40% permethrin Individual Dynamic Absorption (IDA) kit from the US Army’s supply system or water only for sham-treated uniforms. Permethrin treatment is designed to last for 30 washings, which should be suitable for the 6-month duration of the study. At enrollment, each volunteer has one to two field uniforms treated, and civilian volunteers have one to two sets of outer covering garments that they wear while in forested areas treated. The number of clothing sets treated will depend on the number in the volunteer’s possession, and additional clothing sets may be treated during the course of the study if/when the volunteer acquires new clothing, or when treated clothing is damaged or becomes otherwise unserviceable.

Monitoring of treated uniform repellency will be performed by taking uniform swatches numbered with the subject’s study ID at monthly intervals for 6 months. The numbered swatches will be sewn into the uniforms at the time of treatment. Blinded entomology technicians will randomly select 5% of uniform swatches, and place them in cages of female mosquitoes to observe for repellency. The clothing swatches will be placed on the wall of the mosquito cages and proportional landings on the swatch side of the cage will be assessed.

### Sample size rationale

Up to 1200 persons are being enrolled and followed in this cluster-randomized study. The study compares estimates of the absolute risk reduction based on the proportion remaining malaria free at the end of 6 months. We assume that MMP administration combined with an insecticide-treated uniform (ITU) on the background of any pre-existing vector control methods that might be employed will need to reduce malaria incidence to zero by study conclusion to achieve elimination. The MMP approach will be using nearly every currently available intervention in Cambodia to eliminate malaria in this population. Current mathematical models show that multi-round mass drug administration (MDA) can reduce malaria prevalence to less than 10% if high coverage is achieved [27]. Focused screening and treatment alone (FSAT) is assumed to be 50% effective based on a recent study at the same site which found that only 50% of patients treated using an intense screening and treatment approach remained malaria free at the end of 4–6 months of follow-up [2]. The study is, therefore, powered to detect a two-fold difference in effectiveness between the two intervention groups. These are thought to be reasonable assumptions a priori for the purposes of sample size calculations though there has never been a head-to-head comparison of these strategies published in the literature. Given that this will be a stratified analysis, no assumptions regarding vector control measures are included in the calculation. Pre-existing vector control measures that the Military may employ, including ITNs, are assumed to be equally distributed among the overall study population. Permethrin-treated uniform comparisons are a secondary endpoint intended only to estimate a potential additive effect.

Because observations of individuals in the same geographical area (e.g., cluster) are correlated (non-independent), the effective sample size needed is larger than an individualized randomized trial. Given that the intracorrelation coefficient (ICC) is not known, we assumed a conservative value of 0.4. To detect a minimum of a two-fold difference in the effectiveness of MDA over FSAT in proportion of volunteers being malaria-free at 6 months with an α = 0.05 and 80% power, the number needed in each cluster is at least 78 individuals [28]. Given that the number of clusters is limited based on RCAF organization and patrolling areas, our proposed cluster number of 8 with a size of 80–140 volunteers per cluster would be sufficient even at higher (e.g., more conservative) values of ICC (> 0.4).

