### Aim and objectives

We present a pilot operational research protocol to investigate the effectiveness of monthly prophylactic drug administration compared to a focused screen-and-treat approach to inform a regional malaria elimination initiative by the Royal Cambodian Armed Forces (RCAF).*Primary objective*: to compare the effectiveness of focused screening and treatment (FSAT) following current national treatment guidelines versus monthly malaria prophylaxis (MMP) with dihydroartemisinin-piperaquine (DHA-PIP) in combination with weekly primaquine (PQ) (22.5 mg) as transmission-blocking and radical curative agent to reduce the risk of malaria infection in personnel residing in military encampments on the Thai-Cambodian border*Secondary objectives*:◦ To estimate the incremental benefit of wearing a permethrin insecticide-treated uniform (ITU) over drug therapy and existing vector control interventions compared to a sham insecticide-treated uniform (sITU) treated with water. Civilian participants will have comparable selected outer garments treated◦ To define the proportion of asymptomatic carriers of malaria in the population, including the cumulative incidence and incidence density of microscopic and submicroscopic blood-stage parasitemia and gametocytemia◦ Additional secondary objectives can be found in Table 1/Additional file 1

**Table 1 Tab1:** Outcomes

Objectives	Outcomes/endpoints
Primary	
To compare the effectiveness of focused screening and treatment (FSAT) following current national treatment guidelines versus targeted monthly malaria prophylaxis (MMP) with DHA-piperaquine in combination with low-dose weekly primaquine (PQ) (22.5 mg) for 12 weeks	Absolute risk reduction in a cluster based on those individuals’ polymerase chain reaction (PCR)-corrected absence of parasitemia at the end of 6 months in the MMP versus FSAT clusters
Secondary	
Estimate the incremental benefit of insecticide-treated uniforms (ITU) over drug therapy and existing vector control interventions compared to a sham insecticide-treated uniform (sITU)^a^	Absolute risk reduction in a cluster based on those individuals’ PCR-corrected absence of parasitemia at the end of 6 months^a^ Proportional landings of mosquitoes on treated uniform’s swatch side of cages

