### Treatment intervention

Volunteers randomized to MMP arm aged 13 years and older receive a monthly 3-day treatment course of (DHA-PIP; 360/2880 mg) for 3 months. They will also receive a weekly dose of 22.5 mg of PQ for 12 weeks. Children of 12 years of age or less will receive only a monthly 3-day weight-based treatment dose of DP for 3 months without PQ treatment. In the MMP arm, symptomatic patients or microscopy-confirmed parasitemia in the first 3 months are considered a failure of prophylaxis and treatment is given according to the national treatment guidelines. If the volunteer has parasitemia detectable by PCR only and is symptom free at monthly follow-up, the study treatment with monthly DHA-PIP is continued for 3 months as outlined for the MMP arm. To reduce phlebotomy requirements for G6PD testing and potential hemolytic risk in children, PQ is not be administered to those less than 13 years old.

Volunteers randomized to the focused screening and treatment (FSAT) arm are treated according to current national malaria treatment guidelines if they test positive for malaria based on blood smear and/or real-time PCR results during monthly follow-up. In the FSAT arm, all volunteers with parasitemia detectable with PCR receive antimalarial treatment, even if they are symptom- free.

At the time of protocol development, national treatment guidelines for areas of known piperaquine resistance, to include the designated study regions, recommended a 3-day course of artesunate and mefloquine (A + M) and a single 15-mg dose of PQ for acute *P. falciparum*, or DP for blood-stage *P. vivax* infection. Elimination interventions are carried out monthly during the first 3 months after enrollment, and then followed by 3 months of additional malaria assessment by smear and PCR diagnosis with malaria treatment as necessary following current national treatment guidelines (Fig. 1, Table 2, Fig. 2). Those febrile but negative for malaria are referred for evaluation and treatment of alternative diagnoses.

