### Statistical methods

The primary study endpoint will be the absolute risk reduction (ARR) with 95% confidence intervals (CIs) based on the proportion of volunteers in each arm with absence of PCR-positive parasitemia at the end of 6 months using an intention-to-treat analysis (Table 1). In addition, logistic regression modeling may be employed to provide multivariate analyses based on other possible study confounders such as age, proportion of children, proportion of pregnant women, etc. The primary study population will be intention-to-treat, defined as all volunteers (both military and civilian family members) who are enrolled at either site. The per-protocol analysis population will include all those volunteers who enrolled and completed follow-up up to 180 days. However, volunteers lost to follow-up that do not complete up to 180 days of follow-up will be excluded from the per-protocol analysis, but included in an intention-to-treat analysis.

Secondary study endpoints are pilot endpoints to include incidence rates, molecular and parasitological endpoints, safety, vector control effectiveness (e.g., permethrin-treated versus water-treated uniforms), and comparison of malaria and G6PD diagnostic modalities. The calculation of incidence rates (attack rate over total time at risk) for prophylactic and FSAT groups will be calculated adjusted and unadjusted with 95% CI. All volunteers completing at least one follow-up assessment will be included in the safety analysis. The safety analysis database will include those volunteers in the set of randomized volunteers who receive at least one dose of study drug. All parasitological data will be included in the parasitological analyses. A stratified analysis comparing the vector control arms within each group will also be compared as those remaining malaria-free at 180 days. Given the possibility of the highly variable nature of transmission at the geographical sites, existing pre-enrollment malaria surveillance data by RCAF and day 1 screening data by AFRIMS will guide if a pair-matched analysis is necessary.

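### The primary outcome is not fixed as status at 6 months or as freedom from infection over 6 months, and the two planning rates are on different time scales, so the two-fold difference and 80% power are not supported for day-180 status

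*Protocol article*

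**What the plan says.** Three places read most naturally as status at one time point. Table 1 (Aim and objectives) bases the primary absolute risk reduction (ARR) on PCR-"corrected absence of parasitemia at the end of 6 months in the MMP versus FSAT clusters". Statistical methods uses the "proportion of volunteers in each arm with absence of PCR-positive parasitemia at the end of 6 months using an intention-to-treat analysis". The power statement in Sample size rationale refers to a two-fold difference "in proportion of volunteers being malaria-free at 6 months".

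Other places read as cumulative. Sample size rationale opens with "The study compares estimates of the absolute risk reduction based on the proportion remaining malaria free at the end of 6 months". The stratified uniform comparison in Statistical methods also counts those who remain malaria-free to day 180. Limitations frames the hypothesis as overall risk over the study window, and the primary objective is the risk of malaria infection.

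The planning values are both in Sample size rationale. For MMP, incidence has to reach zero by the study's conclusion, supported by a modelled prevalence below 10%. For FSAT, the source is an earlier study in which "only 50% of patients treated using an intense screening and treatment approach remained malaria free" over 4–6 months. The effect is stated only as two-fold; 100% v 50% is implied.

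Under Treatment intervention, every PCR-positive FSAT volunteer is treated, and treatment as needed continues in months 4–6. In MMP, symptomatic or microscopy-confirmed infections in the first 3 months "are considered a failure of prophylaxis and treatment is given according to the national treatment guidelines".

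**The concern.** With monthly PCR and treatment of detected infections, status at day 180 and freedom from infection through day 180 are different quantities. A volunteer infected in month 2, treated and clear at day 180 is a success on the first reading and a failure on the second. That includes an MMP volunteer whom the protocol itself calls a prophylaxis failure. The same data can therefore give two different primary ARRs, and the document does not say which one is the result.

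The sample size inherits the problem. It compares an end-of-study level in one arm with a cumulative proportion in the other, so the two-fold figure is not a contrast on a single outcome.

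**Working it through.** **Inputs from the protocol.** 8 clusters allocated 1:1, so 4 per arm; 80–140 per cluster (midpoint 110 used); ICC 0.4; α = 0.05 (two-sided assumed); 80% power; FSAT 50% over 4–6 months; MMP 100% (implied); monthly PCR.

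**The plan's own figure.** The stated minimum is 78 per cluster. For 50% v 100%, the individually randomized n per arm is 10.5 (pooled variance) or 7.85 (unpooled). With 4 clusters per arm and ICC 0.4 the effective n per arm cannot exceed 4/0.4 = 10. The pooled formula therefore has no solution, and the unpooled one needs only about 6 per cluster. I could not reproduce 78. At 78 per cluster the design effect is 1 + 77 × 0.4 = 31.8 and the effective n is 312/31.8 = 9.8. Power is then 76.8% (pooled z), 87.9% (unpooled z) or 74.3% (t, 6 df). This is a separate matter and does not decide the present point.

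**Step 1: monthly risk.** Assumptions, not in the documents: constant monthly risk h, no one positive at the start, six monthly visits. If 50% stay free over M months, h = 1 − 0.5^(1/M):
- M = 6: 10.9%
- M = 5: 12.9%
- M = 4: 15.9%

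**Step 2: FSAT positivity at day 180.** Let a treated infection be positive at the next visit with probability r + (1 − r)h, where r is the share still or again positive. Running this over six visits:

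| r | M = 6 | M = 5 | M = 4 |
|---|---|---|---|
| 0 | 10.9% | 12.9% | 15.9% |
| 0.1 | 12.0% | 14.2% | 17.4% |
| 0.2 | 13.3% | 15.7% | 19.1% |
| 0.3 | 14.9% | 17.5% | 21.3% |

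With MMP at 100% negative, the ARR equals these values, about 11–21 points. The ratio is 1/0.891 = 1.12 to 1/0.787 = 1.27, not 2.

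**Step 3: longer persistence.** If infections stay detectable for 2 months, FSAT positivity at day 180 is 21–29%; for 3 months, 29–41%. With a 6-month source it reaches 50% only if infections stay detectable for all 6 months. Conversely, if 50% were newly positive at each visit and all were cleared, 1 − 0.5^6 = 98% would be infected at least once. The cited 50% does not imply that.

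**Step 4: power.** SE = sqrt{p(1 − p)[ICC + (1 − ICC)/m]/4}, with MMP variance 0 and m = 110. The lower figure is from a noncentral t with 6 df, the upper from the normal approximation.

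| Contrast | ICC 0.4 | ICC 0.1 | ICC 0.05 |
|---|---|---|---|
| 50% v 100% | 74–88% | – | – |
| 89.1% v 100% | 15–20% | 43–57% | 67–82% |
| 78.7% v 100% | 28–37% | 75–89% | 94–99% |

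For 89.1% v 100% at ICC 0.4, SE = 0.099 and 0.109/0.099 = 1.10. For 50% v 100%, SE = 0.159 and 0.5/0.159 = 3.14.

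**Step 5: the cumulative reading.** Here the FSAT 50% is on the right time scale, but the MMP value is not. Zero incidence by the end does not mean zero infections over 6 months. If MMP were 90% free cumulatively (assumed), the difference would be 40 points and power 44–58% at ICC 0.4 with 78 per cluster.

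**The case against.** Table 1 does not say that only the last visit counts. An absolute risk reduction with absence of parasitemia at the end of 6 months can be read cumulatively, in line with the objective and with Limitations. The several wordings may be loose variants of one intended outcome. This stands. A reader might infer that the planned difference cannot exist on the Table 1 endpoint, but the document does not settle which endpoint Table 1 means. What is shown is that the difference is unsupported if it means day-180 status.

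The conversion to day-180 status rests on assumptions. The cited 50% comes from patients already treated, so recurrence may be common, and clearance by the next visit is not documented. If cluster risks vary (beta-distributed at ICC 0.4, also an assumption), the same 50% gives 15.4% positive for a 6-month source and 21.3% for a 4-month one. ICC 0.4 was itself a planning guess, and a rarer outcome may have a smaller one. So the low end of the range is not a ceiling on the achievable ARR, and the lowest power figures should not be quoted alone.

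End-of-study status is also a defensible outcome for an elimination question, and cumulative incidence is already a secondary outcome. Preferring the cumulative outcome is partly a judgement. A separate analysis plan might fix the counting rule, so it should not be inferred that the team will choose between readings after seeing the data. An analysis plan would not, however, cure the conflicting wording and mixed planning scales in the protocol.

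**Conclusion.** The point holds in this form. The time span of the primary outcome is not fixed, the handling of infections treated before day 180 is unstated, and the two planning rates are on different scales. On day-180 status, the two-fold difference and 80% power are not supported. Under constant risk, 0–30% positive at the next visit and a 4–6 month source, a perfect MMP arm gains about 11–21 points. Power is then 15–37% at ICC 0.4, and reaches 80% only in part of the range at ICC 0.1 or 0.05. Longer persistence would enlarge the difference. These figures are scenarios, not bounds. The conflict in the definition needs none of these assumptions, and because it decides the primary result it should be corrected.

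**What to change.** - Use one primary outcome definition, in identical words, in Table 1, Sample size rationale (both the opening statement and the power statement) and Statistical methods.
- State how an infection found and treated before day 180 counts, in the same way in both arms. The prophylaxis-failure rule covers only symptomatic or microscopy-confirmed MMP cases, so the rule must say explicitly how symptom-free PCR-only positives count.
- Cumulative PCR-positive infection after baseline through day 180 fits the stated objective and uses samples already scheduled, with day-180 status as secondary.
- Put both planning proportions on the chosen scale and restate the detectable ARR and power over a range of ICCs. If day-180 status is kept as primary, withdraw the 50% and two-fold statements.

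Cost: no new samples or visits. The article describes the trial as under way and largely open-label, so this is a substantive protocol amendment, to be made and dated before outcome data are compared by arm. The stated power will be less favourable if the single-visit outcome is kept.

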**Methods/design:**

A two-arm, cluster-randomized controlled, open-label pilot study is being conducted in military personnel and their families at focal endemic areas on the Thai-Cambodian border. The primary objective is to compare the effectiveness of monthly malaria prophylaxis (MMP) with dihydroartemisinin-piperaquine and weekly primaquine for 12 weeks compared with focused screening and treating (FSAT) following current Cambodian national treatment guidelines. Eight separate military encampments, making up approximately 1000 military personnel and their families, undergo randomization to the MMP or FSAT intervention for 3 months, with an additional 3 months’ follow-up. In addition, each treatment cluster of military personnel and civilians is also randomly assigned to receive either permethrin- or sham (water)-treated clothing in single-blind fashion. The primary endpoint is risk reduction for malaria infection in geographically distinct military encampments based on their treatment strategy. Monthly malaria screening in both arms is done via microscopy, PCR, and rapid diagnostic testing to compare both the accuracy and cost-effectiveness of diagnostic modalities to detect asymptomatic infection. Universal glucose-6-phosphate dehydrogenase (G6PD) deficiency screening is done at entry, comparing the results from a commercially available rapid diagnostic test, the fluorescence spot test, and quantitative testing for accuracy and cost-effectiveness. The comparative safety of the interventions chosen is also being evaluated.

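### The sample size section's 78 per cluster does not follow from its stated inputs, and sufficiency above ICC 0.4 has no support beyond about 0.5, even for the largest possible effect

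*Protocol article*

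**What the plan says.** The Sample size rationale sets FSAT at 50% malaria-free. It assumes that MMP must bring malaria to zero, and concludes that the study is powered for a two-fold difference, described as the minimum to be detected. On the ICC it says "we assumed a conservative value of 0.4". It then states that "with an α = 0.05 and 80% power, the number needed in each cluster is at least 78 individuals". It plans eight clusters of 80–140 people each and claims that this design "would be sufficient even at higher (e.g., more conservative) values of ICC". No upper limit on the ICC is given.

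The Abstract gives eight encampments in total, and the randomization section allocates them 1:1, so there are four clusters per arm. The Statistical methods make the primary result an absolute risk reduction with a 95% confidence interval. They name no cluster-level test and leave a pair-matched analysis open. The Limitations accept that the small number of clusters may lower power.

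On clothing, the Abstract says that "each treatment cluster of military personnel and civilians is also randomly assigned to receive either permethrin- or sham (water)-treated clothing in single-blind fashion". The Sample size rationale argues for zero malaria from MMP together with treated uniforms, yet also says that the calculation contains no vector-control assumption.

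**The concern.** This is the only power statement for the primary comparison. With four clusters per arm and a high ICC, information is limited by the number of clusters, so a calculation that answers with people per cluster needs checking. The planned effect also sits at the boundary: nothing larger than 100% malaria-free is possible, and any shortfall costs power. If the stated power is not there, a result that does not separate the arms would be read against 80% power, said to hold under worse correlation as well. MMP could then be judged no better than FSAT on evidence too thin to show it.

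**Working it through.** **Inputs.** From the protocol: FSAT p₁ = 0.50; MMP p₂ = 1.00; ICC ρ = 0.4; α = 0.05; power 80%; k = 4 clusters per arm; m = 80–140 per cluster. Assumed: two-sided α, equal cluster sizes, the same ICC in both arms and no dropout.

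**Step 1: reproduce the 78.** Let n be the number per arm without clustering. The design effect is 1 + (m − 1)ρ. Solving km / [1 + (m − 1)ρ] = n gives m = n(1 − ρ)/(k − nρ).
- Unpooled variance: n = (1.960 + 0.842)² × (0.25 + 0) / 0.50² = 7.85. Then m = 7.85 × 0.6 / (4 − 3.14) = 5.5, or 6 per cluster.
- Pooled variance: n = (1.960 × √0.375 + 0.842 × √0.25)² / 0.25 = 10.5. Then nρ = 4.2, which exceeds 4, so no cluster size works.
- Working back from m = 78: n = 4 × 78 / (1 + 77 × 0.4) = 9.81. Under the unpooled formula this corresponds to MMP of about 97%, not a doubling of 50%.

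One- or two-sided α, a continuity correction and a coefficient-of-variation version do not give 78 on the stated inputs either. The figure 77.9 does arise for 40% versus 80% with eight clusters *per arm*. The protocol states neither input, so that origin is only conjecture.

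**Step 2: the ceiling.** As m grows, km / [1 + (m − 1)ρ] approaches k/ρ. This is 10 per arm at ICC 0.4, 8 at 0.5 and 6.7 at 0.6. At ICC 0.4, m = 80 gives 320/32.6 = 9.82 and m = 140 gives 560/56.6 = 9.89. The unpooled requirement of 7.85 cannot be met above ICC 4/7.85 = 0.51. With pooled variance, power at ICC 0.4 can never exceed 78%.

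**Step 3: power at the planned 100% versus 50%.** At ICC 0.4 and m = 80, SE = √(0.25/9.82) = 0.160, 0.5/0.160 = 3.13, and Φ(3.13 − 1.96) = 88%. The t column spans a noncentral t calculation and a beta-binomial simulation of 20,000 runs. The permutation column is simulated.

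| ICC | Normal, unpooled | Cluster t, 6 df | Exact permutation, m = 80 (m = 140) |
|---|---|---|---|
| 0.4 | 88% | 72–74% | 90% (93%) |
| 0.5 | 80% | 60–65% | 77% (82%) |
| 0.6 | 73% | 49–58% | 61% (66%) |

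Normal quantiles flatter the design: with eight clusters their simulated type I error is about 10% (50% versus 50%, ICC 0.4).

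**Step 4: MMP below 100%, at ICC 0.4.**
- MMP 95%: SE = √(0.2975/9.82) = 0.174 and 0.45/0.174 = 2.59. Power is 73% normal, 58% t and 55% permutation.
- MMP 90%: SE = √(0.34/9.82) = 0.186 and 0.40/0.186 = 2.15. Power is 58% normal, 44% t and 36% permutation.

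The permutation test falls fastest for a simple reason. There are 70 ways to split eight clusters four and four, so its two smallest two-sided p-values are 2/70 = 0.029 and 4/70 = 0.057. It rejects only if every MMP cluster does better than every FSAT cluster.

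**The case against.** The strongest reply has four parts.

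First, on the protocol's own inputs a valid small-sample test does deliver. An exact permutation test respects the eight clusters and has about 90% power at ICC 0.4 and 84% at 0.45. This stands. A reader might infer that 80% power holds only if MMP is perfect and the few degrees of freedom are ignored. The document does not support that. By the unpooled normal formula about 97% malaria-free is enough at ICC 0.4, and the degrees-of-freedom loss applies to a t-based test or interval that the protocol does not name.

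Second, a reader might take 90% malaria-free as the protocol's own figure, because it cites models in which mass treatment "can reduce malaria prevalence to less than 10% if high coverage is achieved", and conclude that true power is 44–58%. That is not supported either. The sentence is background. It gives an upper bound on a modelled prevalence, which is not the proportion remaining malaria-free, and the planning value is 100%. The 90% case is a sensitivity case only.

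Third, this is a pilot, the number of clusters is fixed by military organisation, and the Limitations warn of reduced power. That bears on severity. It does not cure the sample size text: one section warns that power may be short, while the other says the same clusters suffice under stronger correlation.

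Fourth, the uniform wording may be no more than loose drafting. The document does not say how many MMP clusters receive sham-treated clothing, so assuming half would be an inference, and no numerical effect can be shown.

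**Conclusion.** Wrong as written; should-fix. Four things hold.

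1. The 78 per cluster does not follow from 50% versus 100%, ICC 0.4 and four clusters per arm: the formula gives about 6, or no solution.
2. The unbounded sufficiency statement has no support above ICC of about 0.5, even at the planned effect. At 0.6, power is 73% at best and 49–66% with the two small-sample methods. Up to about 0.45–0.50 it can be defended, but only at 100% versus 50% and only with some methods.
3. The effect called a minimum is the maximum possible from 50%. At ICC 0.4, a shortfall to 95% brings power to 55–73%.
4. The Sample size rationale and the Limitations disagree on whether eight clusters are enough.

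These results rest on the assumptions listed in the working. Unequal cluster sizes would lower power slightly, and a pair-matched analysis would leave 3 degrees of freedom rather than 6. The document does not establish that the trial has only 44–58% power; that range belongs to the 90% sensitivity case under the t and normal calculations.

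**What to change.** Keep the eight clusters and rewrite the paragraph.

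- Delete the 78 per cluster, the claim of sufficiency at higher ICC, and the word minimum.
- Give power for four clusters per arm of 80–140 volunteers in a small table: ICC 0.1, 0.2, 0.4 and 0.5, by MMP 100%, 95% and 90% against FSAT 50%. Use the small-sample cluster-level test that the analysis will use, and name it.
- Say that the two-fold difference is the largest detectable effect, and that precision depends on the number of clusters rather than their size.
- State that the MMP planning value is an average over permethrin and sham clusters.
- Align the wording with the Limitations.

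The table would also show where the design is adequate. At ICC 0.2 and m = 80, effective n per arm is 320/(1 + 79 × 0.2) = 19.0. The standardised differences are then 4.36, 3.60 and 2.99, and t-test power (6 df) is about 95%, 85% and 70% for MMP 100%, 95% and 90%.

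The cost is one paragraph and a table, with no extra clusters or volunteers. The downside is that the stated power becomes less favourable.
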